### Confidentiality {27}

The trial staff will ensure that the participants’ anonymity is maintained. The participants will be identified only by the participant’s ID number on the eCRF and any electronic database. All documents will be stored securely and only accessible by trial staff and authorized personnel. The study will comply with the Data Protection Act 1998 which requires data to be anonymized as soon as it is practical to do so.

### Plans for collection, laboratory evaluation, and storage of biological specimens for genetic or molecular analysis in this trial/future use {33}

N/a. No biological specimens will be collected in this study.

## Statistical methods

### Statistical methods for primary and secondary outcomes {20a}

This study constitutes a randomized trial employing repeated measures of a continuous outcome. To address the repeated measures within individuals as delineated by the inclusion criteria (specifically Swedish-speaking females aged 18-50 years diagnosed with BPD), and considering the attendant challenges of collinearity and intra-individual variability, mixed models with individuals as random effects will be employed across various stages of the study (baseline, pre-induction, post-induction, and recovery), as recommended by prior literature [76]. Covariates collected at baseline will be considered, with treatment group, treatment state, and time entered as fixed effects to estimate the effects stemming from the sham/intervention at each time point. The mixed model is versatile, accommodating both continuous and dichotomous outcomes, and will be utilized as deemed appropriate. Given the multitude of potential variables and outcome measures in this study, the necessity for adjustment for multiple tests may arise. To address the issue of multiple testing, we will consider applying the Bonferroni correction, which involves dividing the desired alpha level (typically 0.05) by the number of tests conducted. Alternatively, we may employ false discovery rate (FDR) correction methods to account for the increased risk of false positives when conducting multiple comparisons. The specific method chosen will depend on the final number and nature of outcome measures and variables included in the analysis and will be determined following the completion of the protocol.

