After the baseline assessment has been completed, the transcutaneous electrical vagus nerve stimulation, delivered through a taVNS device (tVNS® R - tVNS technologies, Germany), will start. First, the taVNS device will be described and the taVNS electrode positioned at either the ear concha (active taVNS) or ear lobe (sham taVNS). The device consists of a stimulation unit and an ear electrode that is worn like an earphone. The stimulation unit sends electrical impulses through the electrode, which stimulates a branch of the vagus nerve transcutaneously (through the skin) in the auricle. The device can stimulate at an intensity between a minimum of 0.1 mA to a maximum of 5.0 mA with a biphasic waveform, an impulse duration of 28 s on and 32 s off, and an impulse frequency of 25 Hz. The stimulation intensity will be adjusted for every subject gradually by 0.1 mA at time until a tingling sensation or pulsation can be felt at the stimulation location. The stimulation should be clearly noticeable but not painful or uncomfortable. The device is CE-marked, indicating conformity with European Union regulations for medical devices, for the following conditions: anxiety, asthma, atrial fibrillation, autism, cognitive impairment, Crohn’s disease, depression, epilepsy, fibromyalgia, inflammation, migraines, Parkinson’s, Prader-Willi yndrome, sleep disorders, stroke, tinnitus. However, it is important to clarify that while the device has obtained CE marking, it has not received approval from the FDA or the EMA for the treatment of the listed conditions.

Four minutes after the optimal stimulation dose has been reached, the affect induction procedure will start. The affect induction procedure that will be used in this trial was developed by Daros and colleagues [71]. It has been shown to be tolerable and able to evoke higher negative emotional arousal in BPD patients in comparison with healthy controls [71]. It consists in the presentation on a computer screen of four (one neutral and three affect evoking) 4-min-long videos in sequence, each of which is followed by a 4-min post-induction period during which participants will rate the quality and intensity of the emotions perceived (PANAS) (post-induction ratings) and the perceived effectiveness in managing their emotions (PEME) [32].

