The neutral video depicts a mother attempting to show a father that their young son can play chess and elicited very low levels of emotions in an undergraduate sample [72]. The three negative clips depicted a scene of domestic abuse between a man and a pregnant female partner; a funeral scene where a young girl struggles with the death of her friend; and a scene involving sexual assault by a police officer toward a woman while her husband watches. The domestic abuse clip significantly increased negative mood in a community-sourced sample [73]. The funeral clip elicited sadness in an undergraduate sample, whereas the sexual assault clip elicited anger, disgust, and contempt [72].

The titles and years of production of the films from which the videos are taken are *Searching for Bobby Fischer* (1993; neutral), *Nil by Mouth* (1997; domestic violence), *My Girl* (1991; funeral), and *Crash* (2004; sexual abuse).

After every post-induction period, for the three emotion-inducing videos, the participants will have other 90 seconds to rate again the PANAS (recovery ratings) (see Table 1). The neutral video will be always presented first to allow participants to orient themselves to the procedure. The three affect-evoking videos will be instead presented in a random order using the “randomizer” function of a Qualtrics software [74] (see below). Each page will be locked with a visible timer to ensure that all participants will progress through the procedure at the same pace. If a participant finishes the questions in advance, he/she will be instructed to sit quietly until the next page appears.

At the end of the survey, participants will answer additional questions on the quality of their participation (PQE).

All the instructions, questions, videos, and rating scales will be administered through an online Qualtrics survey [74], with time-fixed auto-advance according to the protocol-defined exposition time for every step of the experiment (see Table 1).

The software IMotions [75] will be used to integrate the data collected from the Qualtrics Survey and from the ECG and GSR sensors.

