### Outcomes {12}

The primary outcome will be the change in negative emotional arousal from baseline, assessed immediately after the affect-induction procedure (post-induction ratings) using the PANAS. Negative emotional arousal will be measured through self-reported ratings of negative emotions on the PANAS (PANAS-N) at five time-points: baseline, after the neutral video, and after each of the three affect-inducing videos (designated as t1, t3, t4, t6, and t8 in Table 1). The means of the PANAS-N scores for each time point will be calculated and used to test the null hypothesis of no difference between the taVNS and sham taVNS groups. A mixed model analysis will be employed to assess each time point separately, ensuring comprehensive evaluation across all time points. The PANAS-N scores have already been used to measure the emotional arousal in previous studies using the same affect induction procedure with BPD patients and have been shown to be able to detect within and between groups differences [28]. The GSR recording, a physiological measure of emotional arousal, will be performed throughout the entire procedure and used to validate the PANAS-N data.

Since an increased emotional reactivity/intensity, one of the three components of the emotional vulnerability together with emotional sensitivity and longer emotional recovery time, is central in the physiopathology of BPD and the underpinning for many of the related symptoms and dysfunctional behaviors (e.g., self-harm) [5], to test the effect of taVNS on this primary outcome may have direct clinical utility. The available psychological treatments are associated with an improvement in the emotional regulation of BPD patients but have uncertain effects on the underlying emotional vulnerability [33].

The secondary outcomes of the study include:Change in negative emotional arousal from baseline at prior to affect induction (pre-induction ratings) as assessed by PANAS.Change in negative emotional arousal from immediately after affect-induction at 4 min after affect induction (recovery ratings) as assessed by PANASPerceived effectiveness in managing emotions (PEME) scores (0–9) during affect induction.

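### The fixed effects listed for the mixed model include no group-by-time term, so they cannot give the per-time-point effects the plan promises; read as main effects, they dilute the treatment effect with the pre-stimulation rating.

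*Protocol article*

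**What the plan says.** All references are to the protocol article.

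- **Statistical methods {20a}.** Mixed models with a random effect for individual "will be employed across various stages of the study (baseline, pre-induction, post-induction, and recovery"). The fixed effects are given "with treatment group, treatment state, and time entered as fixed effects to estimate the effects stemming from the sham/intervention at each time point". No product term appears, and *treatment state* is explained neither here nor elsewhere. On adjustment, the text says only: "Covariates collected at baseline will be considered". Baseline PANAS-N is not named.
- **Outcomes {12}.** "The primary outcome will be the change in negative emotional arousal from baseline", rated on PANAS-N at five points, "designated as t1, t3, t4, t6, and t8 in Table 1". Group means are to be compared at each point, and "A mixed model analysis will be employed to assess each time point separately".
- **Intervention description {11a}.** t1 comes before treatment: "After the baseline assessment has been completed, the transcutaneous electrical vagus nerve stimulation" starts. On order: "The three affect-evoking videos will be instead presented in a random order", so t4, t6 and t8 are positions in the session, not particular films.
- **Sample size {14}.** The calculation counts four post-induction ratings (neutral, funeral, sexual assault, domestic violence). t1 is not among them.

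**The concern.** The sentence in {20a} states both the model terms and their purpose, and the two do not match. Group, state and time as main effects give a single between-arm shift common to all modelled ratings. An effect that may differ between ratings needs a group-by-time term.

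The gap matters more because t1 is one of the modelled ratings. Randomization makes the expected group difference at t1 zero, and a common group coefficient averages that zero in. The reported effect would then be too small and its test would lose power in a trial of 42 people. The t1 rating could instead serve as a covariate and add precision.

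The Outcomes section does not settle the matter. If each time point were fitted in its own model, every participant would contribute one row, leaving no place for time or a random individual effect, both of which {20a} requires. The two sections describe different analyses.

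**Working it through.** **Inputs from the article.** 21 per arm; five primary ratings, one before stimulation; effect size 0.25. I read 0.25 as Cohen's f, which for two equal groups means d = 2 × 0.25 = 0.5.

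**Assumptions.** The article gives neither SD nor correlation. I take SD 1, equal correlation ρ between any two ratings (0.3, 0.5, 0.7), complete data and two-sided 5% tests on 40 degrees of freedom.

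**The plan's own figure.** The article gives no dilution or power figure for this model. Its evaluable N of 34 is not reproduced at G*Power's default settings (ρ 0.5, sphericity 1): four measures and two groups need 24 for the within-person or interaction test and 82 for the between-group test. That is a separate matter and does not decide this point.

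**Step 1: what the group coefficient targets.** With balanced data, a random intercept and main effects of group and categorical time, the group coefficient is the plain average of the group differences over the modelled ratings.

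- Constant effect at t3, t4, t6, t8: (0 + 4 × 0.5)/5 = 0.40, which is 4/5 of 0.5. Simulated mean (150 trials, ρ 0.5): 0.39.
- Effect only at t4, t6, t8: (0 + 0 + 3 × 0.5)/5 = 0.30, which is 3/5. Simulated: 0.30.

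Adding group-by-time to the same data gave contrasts against t1 at t3, t4, t6, t8 of 0.50, 0.50, 0.48, 0.50 in the first case and −0.04, 0.48, 0.47, 0.48 in the second. The true pattern is recovered even though t1 stays a response.

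**Step 2: readings of *treatment state*.**

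- Stimulation off or on for everyone: off at t1, on afterwards, hence the sum of the later time indicators. The design matrix has 7 columns and rank 6. The term cannot be estimated beside categorical time.
- Active stimulation on (0 at t1 in both arms, 1 afterwards in the active arm): its simulated coefficient for a constant effect of 0.5 was 0.495, so t1 causes no dilution. It is still one average over the later ratings, not an effect at each.

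**Step 3: power.** The mean of k ratings has variance v(k) = (1 + (k − 1)ρ)/k. Change from t1 has variance v(4) + 1 − 2ρ. Using t1 as covariate leaves v(4) − ρ². The standard error of the group difference is √(2 × variance/21).

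At ρ = 0.5:
- Main effects including t1: v(5) = 0.60, SE 0.239, 0.40/0.239 = 1.67, power 37%.
- Mean of the four post-induction ratings: v(4) = 0.625, SE 0.244, 0.50/0.244 = 2.05, power 52%.
- t1 as covariate: 0.625 − 0.25 = 0.375, SE 0.189, 0.50/0.189 = 2.65, power 73%.

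| Constant effect, d = 0.5 | ρ 0.3 | ρ 0.5 | ρ 0.7 |
|---|---|---|---|
| Group coefficient, t1 included | 47.9% | 37.2% | 30.6% |
| Mean of t3, t4, t6, t8 | 63.1% | 51.6% | 43.5% |
| Change from t1 | 39.4% | 51.6% | 73.3% |
| t1 as covariate | 72.2% | 73.3% | 84.2% |

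The first two rows isolate the cost of averaging t1 in; the fourth adds the gain from adjustment.

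If the effect exists only after the negative videos, the main-effects coefficient has power of about 30%, 23% and 19%. The mean of t4, t6 and t8 has 58%, 49% and 42%; with t1 as covariate, 66%, 69% and 81%.

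**The case against.** The strongest reply is that silence about an interaction does not establish a main-effects model. Both {20a} and {12} state a per-time-point aim that main effects cannot serve, a journal article condenses, and full model terms often sit in an analysis plan that is not shown here. An unwritten interaction is a likely explanation. This stands: a reader might infer that the trial will certainly report a diluted effect, and the article does not support that. What remains is that the terms as listed contradict their stated purpose and that the two sections do not describe the same analysis.

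Three further replies also stand.

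- A reader might infer that using t1 as a response is itself wrong. It is not. With a group-by-time term, or with arm means constrained equal at t1, it is a valid model. The fault is t1 as a response without either. Nor is adjustment for t1 PANAS-N excluded, since baseline covariates are to be considered; it is only not named.
- A reader might take 23% against 69% as the price of the missing interaction. That comparison assumes no effect at the neutral video, and it both drops ratings from the outcome and adds a covariate. The sample-size section counts the neutral video as an outcome measure, so the constant-effect figures are the fairer headline. The dilution also depends on the rows used: if all nine ratings t1 to t9 entered one model, a constant effect would be scaled by 8/9, not 4/5.
- Omitting video identity causes no bias, because the order is random. Every completer sees all three negative videos, so video means cancel in the average over t4, t6 and t8.

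**Conclusion.** The concern holds in a limited form. The fixed effects listed in {20a} cannot give the effect at each time point that the same sentence and {12} promise; *treatment state* is undefined and on one natural reading cannot be estimated; and the two sections need reconciling.

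The dilution is conditional. On a main-effects reading of the five primary ratings, the group coefficient is 4/5 of a constant effect, or 3/5 if the effect follows only the negative videos. Power for the constant effect is then about 48%, 37% and 31% at ρ 0.3, 0.5 and 0.7, against 72%, 73% and 84% with t1 as covariate. These figures rest on d = 0.5, 21 per arm with complete data, and correlations the article does not give. The dilution by t1 disappears if a group-by-time term was intended or if *treatment state* marks active stimulation over time. The advantage of adjusting for t1 over the main-effects model holds at every correlation tried; that of a plain change score does not (39.4% against 47.9% at ρ 0.3).

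**What to change.** Replace the two descriptions in {12} and {20a} with one model:

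- Outcome: PANAS-N at t3, t4, t6 and t8, with individual as random effect.
- Fixed effects: group, time as a category, group-by-time, and PANAS-N at t1 as covariate. Alternatively, keep t1 as a response and constrain the arm means to be equal there.
- Define *treatment state* or drop it.
- Name one primary contrast over the post-induction ratings, stating whether the neutral video counts. Effects at single ratings then follow from the same model.

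A term for video identity is optional. It can sharpen comparisons at a single position but is not needed for the average over t4, t6 and t8 in completers.

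The cost is wording in the protocol or analysis plan, settled before the data are analysed. The t1 rating is already collected, and the survey software already assigns the video order.

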### Interim analyses {21b}

No interim analysis is planned.

### Methods for additional analyses (e.g., subgroup analyses) {20b}

The sample is small, so no subgroup analyses are planned a priori.

### Methods in analysis to handle protocol non-adherence and any statistical methods to handle missing data {20c}

In case of missing response to the PANAS at any post-induction stage, a mean value of other post-induction stage measurements will be used. Since the study is a single-session study under clinician oversight, we do not expect any missing variables.

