### Criteria for discontinuing or modifying allocated interventions {11b}

Each participant has the right to withdraw from the study at any time. In addition, the investigator may discontinue a participant from the study at any time if the investigator considers it necessary for any reason, including ineligibility (either arising during the study or retrospective having been overlooked at screening), significant protocol deviation, significant non-compliance with study requirements, an adverse event which requires discontinuation of the taVNS or results in inability to continue to comply with study procedures, emotional crisis which results in inability to continue to comply with study procedures or consent withdrawn.

The reason for withdrawal will be recorded in the electronic Case Report form (eCRF) (Qualtrics module) and in a research note in the patient research diary. If the participant is withdrawn due to an adverse event, the investigator will arrange for follow-up visits or telephone calls until the adverse event has resolved or stabilized.

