### Sample size {14}

We are going to recruit 42 participants (21 participants per arm). The total sample size has been calculated using G*Power 3.1 Software to test an effect size of 0.25 with a power (1−*β*) = 0.8 for a sample with two independent groups (taVNS vs Sham-taVNS) and 4 dependent measures (PANAS-N score post-induction for neutral, funeral, sex-assault and domestic violence videos). The sample size needed is *n* = 34, calculated with an alpha level of 0.05. With an expected level of attrition of about 20%, the sample size has been increased by a factor of 1/(1–0.2) = 1.25 or 25% to 42 subjects.

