#### Self-reported rating measures

The primary outcome will be measured through the PANAS [27]. Before undergoing the taVNS and affect induction procedure, (“baseline” or t1), after 4-min taVNS and before the first video (“preinduction” or t2), and after each video (“postinduction” or t3, t4, t6, and t8), participants will be asked to provide affect ratings using the 20-item PANAS [27] (Table 1). The scale uses adjectives that describe mood states rather than discrete emotions and are rated from 1 = very slightly or not at all to 5 = extremely. The PANAS is used widely in mood induction procedures because of its good validity and test–retest reliability. At postinduction, participants provided self-report ratings on six basic emotions felt in response to each video (disgust, fear, anger, sadness, happiness, and surprise) on a scale from 1 = not at all to 7 = extremely. A total of 4 min after each negative video, participants provided another set of PANAS ratings to measure changes in mood over a longer period (“recovery” or t5, t7, and t9). The PANAS is a reliable and valid measure of the construct it is intended to assess [37].

Moreover, participants will be asked during postinduction about their perceived effectiveness in managing their emotions (PEME) by asking them to rate “How difficult was it to manage your emotional response to this film clip?” from 1 = not at all to 9 = extremely. This scale will be interpreted as a subjective difficulty in regulating emotions in response to each video stimulus.

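### A missing post-induction PANAS is filled with a mean that includes the neutral video, so an imputed negative-video rating comes out too low; applied to participants who stop early, the rule favours the arm that loses more of them

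*Protocol article*

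**What the plan says.** The missing-data section {20c} fixes one rule: "In case of missing response to the PANAS at any post-induction stage, a mean value of other post-induction stage measurements will be used". It adds that, because this is a single supervised session, "we do not expect any missing variables".

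Three other sections show what the rule averages over. Self-reported rating measures lists the ratings made "after each video (“postinduction” or t3, t4, t6, and t8", and t3 is the rating after the neutral video. Sample size {14} counts "4 dependent measures (PANAS-N score post-induction for neutral, funeral, sex-assault and domestic violence videos". Outcomes {12} takes the primary outcome at "baseline, after the neutral video, and after each of the three affect-inducing videos". No section removes the neutral rating from the imputation mean.

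Intervention description {11a} puts the neutral video first for everyone and says that it "elicited very low levels of emotions in an undergraduate sample". The order of the three negative videos is random.

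On incomplete participation, Criteria for discontinuing {11b} lists among its reasons an "emotional crisis which results in inability to continue to comply with study procedures", and Sample size {14} inflates the target with the words "With an expected level of attrition of about 20" per cent.

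**The concern.** The neutral rating is the post-induction score most certain to exist when someone stops at a negative video, and by design it is the lowest. Averaging it in pulls a missing negative-video score towards the neutral level. A participant who stops at the first negative video has only t3, so the neutral score is copied into all three negative stages.

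The affected quantity is the primary outcome, negative affect after induction. Becoming too distressed to go on is a foreseen reason for stopping and is related to that outcome. If such participants are imputed, an arm is credited with lower negative affect for each one it loses. The filled-in values would also be analysed as if they had been observed. A filled t4, t6 or t8 enters the recovery outcome too, since recovery is measured as change from those ratings.

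**Working it through.** **Attrition figure.** 34/(1 − 0.2) = 42.5, which the protocol takes as 42. So 42 − 34 = 8 participants are allowed for. The missing-data rule itself carries no figure to reproduce.

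**Error per imputed rating.** Let N be the mean PANAS-N after the neutral video, V the mean after a negative video (taken as equal for the three), D = V − N, and k the number of negative videos rated before stopping. The rule imputes (N + kV)/(k + 1). Subtracting V gives an error of −D/(k + 1). The sign requires only that negative videos score above the neutral one, which is the purpose of the induction.

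| k | Imputed value | Error per imputed rating | Ratings missing | Error in that person's mean over three negative videos |
|---|---|---|---|---|
| 0 | N | −D | 3 | −D |
| 1 | (N + V)/2 | −D/2 | 2 | 2 × (−D/2)/3 = −D/3 |
| 2 | (N + 2V)/3 | −D/3 | 1 | (−D/3)/3 = −D/9 |

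This supposes that the missing rating would have been average. If it would have been higher, the error grows by the excess. For example, with D assumed to be 8 points the errors per rating are 8.0, 4.0 and 2.7. If the missing rating would have been 5 points above average, they are 13.0, 9.0 and 7.7.

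**False difference under the null.** This is the difference in stopping proportions times the per-person error. Assume 10% stopping under taVNS and 30% under sham (about 2 and 6 of 21), and summarise by the mean over the three negative videos. D is not in the documents, so a range is shown, in SD units:

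| Stopping pattern | Formula | D = 1 | D = 1.5 | D = 2 |
|---|---|---|---|---|
| Only t8 missing | 0.2 × D/9 | 0.02 | 0.03 | 0.04 |
| After the first negative video | 0.2 × D/3 | 0.07 | 0.10 | 0.13 |
| At the first negative video | 0.2 × D | 0.20 | 0.30 | 0.40 |

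Here sham loses more and sham looks better. Reverse the imbalance and taVNS looks better by the same amount.

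**With a true effect of −0.50 SD at the negative videos** (taVNS minus sham, D = 1.5 SD in the sham arm):
- 20% in each arm stop at the first negative video, no effect at the neutral video: 0.8 × (−0.50) = −0.40.
- Same stopping, effect also −0.50 at the neutral video: 0.8 × (−0.50) + 0.2 × (−0.50) = −0.50, so no shrinkage.
- 10% versus 30% stop at the first negative video, no effect at the neutral video: 0.9 × 1.0 − 0.7 × 1.5 = −0.15.
- 10% versus 30% with only t8 missing: between −0.46 (no effect at the neutral video) and −0.47 (same effect there).

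**Stopping linked to distress.** A simulation assumed D = 8 points, SD 7, within-person correlation 0.5, stopping that rises moderately with distress, and no true effect. The arm mean was too low by 1.56 points with 30% stopping and by 0.51 with 10%. The false difference is 1.05 points, or 1.05/7 = 0.15 SD.

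**Would dropping only t3 from the mean suffice?** No. In the simulations this removed the error for k = 1 or 2 when stopping was unrelated to distress. When stopping rose with distress, an understatement of about 2 to 4 points per imputed value remained. For k = 0 there is no negative rating to average.

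**The case against.** **Scope.** The rule speaks of a missing response, and the article does not say whether discontinued participants are imputed or excluded. Inflating 34 to 42 may mean that those lost are left out of the analysed set. The reasons for discontinuation also include late-found ineligibility, protocol deviation and withdrawn consent, so the 20% is not all distress. This stands. A reader might infer that 20% attrition flatly contradicts the expectation of no missing data. The two can be squared if attrition means exclusion, but the article does not say so. Even on the narrow reading, one skipped negative rating with the other two present is filled D/3 too low.

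**Equal stopping.** A reader might infer that the rule always dilutes the effect. The documents do not support that. Stimulation starts before the neutral video, and one secondary objective is to lower arousal before any induction, so an effect at t3 is possible. Dilution under equal stopping needs a smaller effect at t3 than at the negative videos. Equal stopping with no true effect produces no false difference.

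**Size.** A reader might take 0.30 SD as the expected bias. It requires an assumed D, a threefold imbalance in stopping, and every dropout occurring at the first negative video. Nothing in the article supports that pattern. The article calls the procedure tolerable, and the description of the neutral clip comes from undergraduates, whereas it reports raised resting arousal in BPD.

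**The mixed model.** A reader might infer that the planned model already makes imputation unnecessary. A joint longitudinal model would, but Outcomes {12} speaks of assessing time points separately, so a joint model is not settled. A joint model also relies on missing at random. Someone who stops during the first negative video leaves no negative rating to inform it, so it too can understate distress.

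**Conclusion.** The rule as written is wrong in a known direction: a negative-video rating imputed from a mean that includes the neutral score is too low on average by D, D/2 or D/3. That follows from the article's own definitions and the purpose of the induction.

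The effect on the treatment comparison is conditional. It arises if participants who stop early are imputed, and it favours the arm that loses more of them. At an assumed D of 1.5 SD and 10% versus 30% stopping, the false difference under the null runs from about 0.03 to 0.30 SD according to when participants stop, and it scales in proportion to D. These figures are illustrations, not forecasts. They use the mean over the three negative videos, which the article does not fix as the single summary. The rule still needs correcting, because it acts on the primary outcome and brings no gain over a joint model of the observed ratings.

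**What to change.** 1. Delete the imputation rule from the missing-data section {20c}.
2. Specify one joint likelihood-based mixed model for PANAS-N at t1, t3, t4, t6 and t8, using all observed ratings of all randomised participants, with arm, video/time and their interaction. State that it assumes missing at random, and align the separate-time-point wording in Outcomes {12} with it.
3. Add a delta-adjusted multiple-imputation sensitivity analysis. Unobserved negative-video ratings after distress-related stopping are shifted upward over a range fixed in advance, with the shift varied separately by arm. Multiple imputation keeps the filled-in values from being treated as observed.
4. Say whether participants who discontinue stay in the analysis, and reconcile the expectation of no missing variables with the 20% attrition in Sample size {14}.

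The cost is a few sentences of analysis text and one sensitivity analysis, with no change to trial conduct. The reason for stopping, which step 3 needs, is already to be recorded in the eCRF. The change should be made before the data are analysed.
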